#### Sample size

Sample size was calculated for the main study variables, 5STS and HG. The minimum detectable change in similar populations and interventions was 2.5 points (a decrease in 5STS and an increase in HG) to consider a real change beyond measurement error [30, 31]. The study used GRANMO version 7.12 of April 2012. Assuming three groups, with an alpha risk of 0.05 and a beta risk of 0.2 in a bilateral contrast. A loss-to-follow-up rate of 20% was estimated, given that the intervention was extensive and older people are known to have lower adherence to physical activity programs [32]. It was concluded that 105 subjects would be needed among the three groups with a 1:1:1 ratio to detect a difference equal to or greater than 2.5 units, assuming a standard deviation of 5 units.

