### Data analysis

Statistical analysis will be performed using an intention-to-treat (ITT) approach. Baseline differences between groups will be tested using normality plots and the Kolmogorov-Smirnov test. Homogeneity between groups will be assessed using Levene’s test, thus ensuring successful randomisation. Missing data will be handled using the imputation method of the last observation carried forward. It will be decided to keep outliers in the analysis, as they may represent legitimate outliers or relevant information, which will be discussed in the future study.

A descriptive analysis of the dependent and independent variables of each group will be carried out. Quantitative variables will be expressed as mean ± standard deviation, while qualitative variables will be presented as frequency distributions and percentages.

To assess the effect of the interventions on the study variables in each group, multivariate analysis of variance (MANOVA) will be used as the main method. The variables will be grouped into two large blocks: those measuring functionality (HG, 5STS, GS, TUG, Two-minute step test and SPPB) and those measuring body composition (weight, WC, BF%, visceral fat, ASM, SMI and BMI). Subsequently, MANOVA will be performed on the difference in means after the intervention, using time as an intra-group factor and type of intervention as an inter-group factor. To graphically represent the MANOVA, the canonical Biplot will be displayed, including the confidence circles representing the set of variables in each intervention group. If the circles do not overlap, it can be concluded that there are significant differences between the groups.

To verify the results of the MANOVA, differences between groups for each quantitative variable, both functional and body composition, will be analysed using the repeated measures univariate analysis of variance (ANOVA) test for normal and homogeneous variables or the Kruskal-Wallis test for non-normal or heterogeneous variables. As an additional method, pairwise comparisons will be performed using Bonferroni’s test for normal and homogeneous variables and Dunn’s test for non-normal and heterogeneous variables to determine between which groups there are significant differences.

The effect size in ANOVA of the results obtained in each group will be measured by eta squared (η^2^). Values around 0.01 indicate a small effect size, around 0.06 a medium effect size, and 0.14 or more a large effect size.

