A 95% confidence interval will be used to establish any differences, and statistical significance will be reported for all differences with p < 0.05 (bilateral). All statistical analyses will be performed using IBM SPSS for Windows (version 26.0, Armonk, NY. IBM. Corp.).

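### Concluding significance from non-overlapping biplot circles is not equivalent to the protocol's 0.05 test and can contradict the MANOVA it is meant to illustrate

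*Protocol article*

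**What the plan says.** All of this is in the protocol article, under Data analysis unless noted.

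- Main method: "multivariate analysis of variance (MANOVA) will be used as the main method", run on two blocks of outcomes. The functional block has six variables and the body composition block seven.
- Role of the figure: "To graphically represent the MANOVA, the canonical Biplot will be displayed, including the confidence circles representing the set of variables in each intervention group".
- Decision rule, in the next sentence: "If the circles do not overlap, it can be concluded that there are significant differences between the groups".
- Follow-up: repeated-measures ANOVA or Kruskal-Wallis for each variable, then Bonferroni or Dunn pairwise comparisons to locate the differences.
- Level: two-sided 0.05, and "A 95% confidence interval will be used to establish any differences". The 95% level is stated in general and is not tied to the circles.
- Size, under Sample size: "105 subjects would be needed among the three groups with a 1:1:1 ratio", so 35 per group.

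The section gives no radius, confidence level or pair correction for the circles, and it does not make the rule conditional on the MANOVA result.

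**The concern.** The paragraph contains two criteria for the same question. One is the MANOVA P value at 0.05. The other is whether circles on a plot touch. Three features separate them.

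1. Non-overlap of two equal circles needs a distance above r + r = 2r. A test of the difference between two equal-sized groups needs about √2 times r. A full multivariate radius therefore makes the rule far too strict.
2. With three groups the canonical plane has two dimensions and carries all the between-group separation across six or seven variables. A radius built for one or two dimensions ignores this and makes the rule far too lax.
3. Three pairs can be inspected. The Bonferroni and Dunn corrections are attached to the univariate comparisons, and the text does not extend them to the circles.

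At stake is a statement that power training differs from multicomponent training or from no exercise, drawn from the plot although the main test does not support it. The reverse can also happen: circles that touch after a significant MANOVA. The protocol does not say which criterion prevails.

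**Working it through.** **Inputs from the protocol.** Three groups; 105/3 = 35 per group; p = 6 and p = 7 variables; level 0.05, two-sided. The analysis is by intention to treat with last observation carried forward, so 35 per group is the natural analysis size. With the stated 20% loss, 35 × 0.8 = 28 per group. The protocol states no error rate for the circle rule, so there is no figure to reproduce first.

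**Assumptions.** One multivariate normal vector of changes per participant, equal covariances, equal group sizes, independent participants, no true effect. The radius is my assumption, so a range is shown.

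**One-variable illustration.** Two separate 95% intervals of equal width fail to overlap when the difference exceeds 2 × 1.96 standard errors of a mean. That is 1.96 × √2 = 2.77 standard errors of the difference, a two-sided P of 0.0056 and not 0.05.

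**Rule in the canonical plane.** The distance D between two group points is the Mahalanobis distance with the pooled within-group covariance, with df = 105 − 3 = 102. Circles of radius r/√n do not overlap when D > 2r/√n. For a single pair T² = nD²/2, so non-overlap means T² > 2r². The exact single-pair rate then follows from F = T²(df − p + 1)/(df × p) on p and df − p + 1 degrees of freedom.

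- t radius, p = 6: r = 1.983, T² > 7.87, F = 7.87 × 97/(102 × 6) = 1.247, rate 28.9%.
- Multivariate F radius, p = 6: r = √(6 × 102/97 × 2.194) = 3.720, T² > 27.68, F = 4.387, rate 0.06%.

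For p = 7 the same steps give 39.7% and 0.04%.

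**At least one of the three pairs separated.** Null simulation, 35 per group:

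| Assumed radius | r (p = 6 / p = 7) | p = 6 | p = 7 |
|---|---|---|---|
| t, one variable | 1.983 / 1.983 | 56.1% | 69.3% |
| Chi-square, 2 df | 2.448 / 2.448 | 21.2% | 31.6% |
| Bonferroni-t over p variables | 2.691 / 2.745 | 10.5% | 14.8% |
| Bonferroni-t over 3p | 3.066 / 3.116 | 2.8% | 4.4% |
| Multivariate F | 3.720 / 3.958 | 0.18% | 0.11% |

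A rate of exactly 5% would need r of about 2.91 (p = 6) or 3.08 (p = 7). At 28 per group the t and F figures are 56.6% and 0.19% (p = 6), and 70.3% and 0.15% (p = 7).

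**Against the MANOVA.** A second null simulation (60,000 runs, 35 per group) computed Wilks' test on the same data. Wilks rejected in 4.9% (p = 6) and 5.0% (p = 7) of runs.

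| Assumed radius | Circles separate, MANOVA not significant (p = 6 / p = 7) | Circles separate and MANOVA significant (p = 6 / p = 7) |
|---|---|---|
| t | 50.5% / 64.6% | 4.9% / 5.0% |
| Chi-square, 2 df | 16.0% / 26.8% | 4.9% / 5.0% |
| Bonferroni-t over p | 5.9% / 10.0% | 4.5% / 4.9% |
| Bonferroni-t over 3p | 0.5% / 1.3% | 2.4% / 3.2% |
| Multivariate F | 0.0% / 0.0% | 0.2% / 0.1% |

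With the F radius the conflict runs the other way: among null runs with a significant MANOVA, about 96% (p = 6) and 97% (p = 7) show no separated pair.

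**The case against.** The best defence is the structure of the plan. MANOVA is the main method, the biplot is introduced to depict it, and univariate tests with adjusted pairwise comparisons follow. On that reading the criticised sentence is only guidance for a figure that accompanies a significant MANOVA. This has force. If the circles are read only after a significant MANOVA, a false conclusion under the global null cannot be more frequent than the MANOVA's own error, about 5%.

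Two limits remain. The sentence itself contains no such condition. And the condition protects only the global null: once a real difference between one group and the others makes the MANOVA significant, the remaining pair would still be judged by circles. With t radii that pair would separate by chance in about 29% (p = 6) or 40% (p = 7) of trials.

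The second defence is that the radius is not given, so any single rate is conditional, and a condensed article may leave that detail to a fuller plan. That also stands. The range shows how far the rule depends on an unstated choice.

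Stronger readings are tempting but not supported. A reader might infer that the trial has a false-positive rate of 56% or 70%. That needs t radii and circles read alone, against a non-significant main test. A reader might also infer that the three pairs go uncorrected. The protocol is silent on this, and a radius corrected for variables and pairs (Bonferroni-t over 3p) keeps the rate below 5%.

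**Conclusion.** The point holds in a limited form. The protocol licenses a conclusion of significant differences from non-overlapping circles, without a MANOVA condition, a radius or a stated correction for three pairs. That is not equivalent to its 0.05 criterion. Read alone, under the assumed 95% radii, the null error runs from about 0.2% to 56% for the functional block and from about 0.1% to 70% for the body composition block. Disagreement with the main method can be common: with t radii, about 50% to 65% of null trials show separated circles and a non-significant MANOVA. Read only after a significant MANOVA, the global null error stays at or below about 5%.

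The figures assume normality, equal covariances, equal group sizes and independent participants. Clustering was not modelled, although the Design and setting section says that eligible women from one senior centre are grouped together and randomly assigned. It would generally raise these rates.

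This is a wrong inference rule attached to a supplementary figure. It is worth correcting but does not undermine the main analysis.

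**What to change.** Delete the decision sentence. In its place state that the canonical biplot and its circles are descriptive only. State that between-group differences are concluded from the MANOVA P value for each block, followed by the univariate tests and the Bonferroni or Dunn pairwise comparisons already planned. MANOVA stays the main method.

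The cost is a change of wording. No new data or analysis is needed, and the figure can still be shown.

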**Methods:**

A randomized controlled trial will be conducted with three parallel groups: a PT group, a multicomponent training (MT) group, and a no-exercise group. The inclusion criteria will be women over 65 years of age who meet the diagnostic criteria for probable sarcopenia (Hand grip test less than 16 kg and Five Times Sit to Stand Test more than 15 s) according to the European Working Group on Sarcopenia in Older People (EWGSOP2). Two assessments will be conducted at the beginning and at the end of the 32 weeks of intervention, in which variables of body composition (muscle, fat and weight) and functionality (strength and physical performance) will be collected. There will be 3 sessions of 50 minutes per week in each intervention group. The masking strategy will be double-blind. The analysis of intergroup differences will be conducted using multivariate and univariate analysis of variance (MANOVA and ANOVA), as well as pairwise comparisons (Bonferroni corrections). Changes in the degree of sarcopenia and how many women eliminate the risk of sarcopenia (no probable sarcopenia) after the different interventions will be tested.

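### The only normality and variance checks described are baseline checks; if, as the text reads, they choose the univariate outcome test, they can choose wrongly

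*Protocol article*

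**What the plan says.** All the relevant analysis text is in the Data analysis section of the protocol article.

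- Normality: "Baseline differences between groups will be tested using normality plots and the Kolmogorov-Smirnov test".
- Homogeneity: "Homogeneity between groups will be assessed using Levene’s test, thus ensuring successful randomisation". The word baseline is not repeated, but a check on randomisation only makes sense for data collected before the intervention.
- Omnibus test: the "repeated measures univariate analysis of variance (ANOVA) test for normal and homogeneous variables or the Kruskal-Wallis test for non-normal or heterogeneous variables".
- Pairwise tests: "Bonferroni’s test for normal and homogeneous variables and Dunn’s test for non-normal and heterogeneous variables". The omnibus rule joins the two failures with *or*, the pairwise rule with *and*. A variable that fails only one check therefore has an omnibus test but no clear pairwise test.
- Place in the analysis: "multivariate analysis of variance (MANOVA) will be used as the main method". The univariate tests are there to verify it, and the pairwise tests are an additional step.

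Elsewhere, the abstract's Methods make entry conditional on "Hand grip test less than 16 kg and Five Times Sit to Stand Test more than 15 s". These are also the primary variables: "Sample size was calculated for the main study variables, 5STS and HG". The Evaluations section places the baseline assessment before randomisation.

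**The concern.** The assumptions of an ANOVA concern the residuals of the model fitted to the outcome, here the change to week 32 or the baseline-adjusted final value. The shape and spread of baseline values can mislead about both.

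- **Normality.** Women enter only on one side of each cut-off, so baseline HG is cut off above 16 kg and baseline 5STS below 15 s. A baseline test may find this skew even when change is perfectly normal. The two primary variables would then go to rank tests, which have no time factor and give no mean difference in kg or seconds. The sample size rests on a mean difference of 2.5 units.
- **Variance.** Before randomisation the arms differ in spread only by chance. Levene's test there cannot detect unequal spread that develops when two arms train and one does not. Other variables could then keep a pooled SD that includes the control arm, and this affects the PT versus MT contrast.

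**Working it through.** The plan gives no figure on this point to reproduce. Its sample size section supplies SD 5, a difference of 2.5, and 105 women in three equal groups. That is 105/3 = 35 per arm, or 35 × 0.8 = 28 after the 20% loss. Everything else is an assumption, shown as a range. All simulations treat women as independent, although allocation appears to be by senior centre.

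**1. What feeds the rule.** The section describes one normality check and one homogeneity check, both worded as above. The rule then uses the same two properties and names no other data. The link between them is the plain reading, but it is not stated.

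**2. Normality at baseline.** HG was drawn from a normal distribution with mean 14-22 kg and SD 5, kept between 5 and 16 kg. 5STS was drawn from normals with mean 13-18 s and SD 5, or mean 12 s and SD 3, kept above 15 s. The table shows how often Kolmogorov-Smirnov rejects normality at 5%.

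| | HG | 5STS |
|---|---|---|
| Skew | -0.4 to -1.2 | 0.8 to 1.3 |
| Lilliefors version, all 105 pooled | 60-99.7% | 66-99% |
| Lilliefors version, one group of 35 | 18-61% | 21-62% |
| Lilliefors version, at least one of three groups | 48-95% | 57-93% |
| Uncorrected, all 105 pooled | 4-59% | 5-57% |
| Uncorrected, one group of 35 | 0-4% | 0-4% |

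With normal change scores, the Lilliefors test on the change residuals rejects in 3-4%, close to the nominal rate. The screen can therefore fail a variable whose outcome model is sound. How often depends on pooling and on the version of the test, and the article gives neither.

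**3. Variance at baseline.** With 35 per arm, truncated baselines and equal true variances, Levene's test (mean-centred) rejects in 10-11% of trials, whatever happens later. On change scores with SD ratios 1:1:1.5 and 1:1:2 it rejects in 62% and 97%.

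**4. Power cost of moving to ranks.** With two time points, the group-by-time test of a repeated-measures ANOVA is the one-way ANOVA on change, so that is the comparator. Baseline is truncated, change is normal, one arm differs by 2.5, and there are 35 per arm.

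| SD of change | ANOVA on change | Kruskal-Wallis on change | Kruskal-Wallis on final values |
|---|---|---|---|
| 3 | 95.6% | 94.4% | 75.2% |
| 5 | 54.6% | 52.3% | 42.7% |

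The loss is 1.2 and 2.3 points on change, and 20.4 and 11.9 points on final values. A second set-up (28 per arm, effects 2.5/1.25/0) gave 78%, 75% and 62%.

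**5. PT versus MT error with a pooled SD.** Assume change SDs of 5, 5 and *s* (control), 28 per arm, and a test at 0.05/3 = 1.7%. The critical t on 81 degrees of freedom is 2.445. The pooled variance is (25 + 25 + s²)/3, and the approximate error is P(|Z| > 2.445 × pooled SD/5).

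- s = 2.5: 56.25/3 = 18.75, SD 4.33; 2.445 × 4.33/5 = 2.117; error about 3.4%.
- s = 4: 66/3 = 22, SD 4.69; 2.445 × 4.69/5 = 2.293; error about 2.2%.

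Simulation (200,000 trials), which lets the pooled SD vary, gives:

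| s | PT-MT | Each control contrast | Family-wise | Welch PT-MT |
|---|---|---|---|---|
| 2.5 | 3.9% | 0.9% | 4.9% | 1.7% |
| 4 | 2.4% | 1.3-1.4% | 4.5% | 1.7% |

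**6. Omnibus error.** With SD ratio 1:1:2 and equal groups it is 5.7% for ANOVA and 5.1% for Kruskal-Wallis. It becomes large only when arm sizes are unequal too: with 35/35/20 and the smallest arm the most variable, 11.3% and 7.6%.

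**The case against.** The article never states that the baseline checks choose the outcome test, and the Levene sentence does not name baseline. Which data an assumption check uses could be settled in a fuller document. This is fair, and the link must be presented as an inference. It does not remove the point. The article describes the rule and the only checks that could feed it, and a reader who follows it as written would use baseline data.

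A reader might infer more than the documents support:

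- *That the rule always picks the wrong test.* Truncation makes the baseline population non-normal, but a test on 35 women often misses it, and the normality plots leave room for judgement. Variances are equal at baseline only in expectation.
- *That HG and 5STS lose their mean-based analysis.* The MANOVA is the main method, includes both variables, works on mean differences and is not subject to the screen.
- *That false positives rise overall.* The assumed smaller control SD is not in the documents. Even with it, error moves from the control contrasts to PT versus MT, and the family-wise rate holds.
- *That both harms fall on the same variables.* A variable sent to Kruskal-Wallis and Dunn does not reach the pooled Bonferroni test, so the variance problem falls mainly on secondary variables.
- *That power falls by 12 points or more.* This holds only if ranks are applied to final values, which the article does not say.

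**Conclusion.** The point holds in a limited form. As worded, the choice between mean-based and rank-based univariate tests rests on baseline data, which cannot show whether the outcome model's assumptions are met. The rule can, but need not, send HG and 5STS to rank tests and keep a pooled SD for other variables.

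The direct numerical cost is modest under the assumptions shown: about 1-3 points of power on change scores, and a PT versus MT error of 2.4-3.9% against 1.7% if the control SD is 2.5-4 rather than 5. The more practical loss is that a primary variable moved to ranks has no univariate estimate in kg or seconds, although the section says 95% confidence intervals will be used to establish differences. The MANOVA is untouched. However, the univariate and pairwise steps are the ones that test each variable and each pair of arms, so the change is worth making.

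**What to change.** Reword the Data analysis section as follows.

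1. State that the baseline Kolmogorov-Smirnov and Levene results will not be used to choose the outcome test.
2. Judge assumptions on the residuals of the week-32 model, for change or the baseline-adjusted final value.
3. Keep HG and 5STS in that mean-based model whatever their baseline shape, and report differences in kg and seconds with 95% confidence intervals.
4. Use Welch or heteroscedasticity-robust standard errors for the pairwise contrasts, with the Bonferroni adjustment kept.
5. Keep Kruskal-Wallis and Dunn as sensitivity analyses, and name the quantity ranked. This also removes the mismatch between *or* and *and* in the two selection rules.

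The cost is wording only, with no new data. If variances are in fact equal, Welch loses very little: with 28 per arm, SD 5 and a test at 0.05/3, simulated power for one contrast falls from 28.8% to 28.2% at a difference of 2.5, and from 90.0% to 89.4% at a difference of 5.

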**Discussion:**

The study aims to investigate the impact of PT in older women at risk of sarcopenia. The expected results are that PT will significantly improve functionality and body composition compared to other forms of exercise (MT) and no physical activity. The results may represent a significant advance in understanding and addressing sarcopenia before it becomes established, providing preventive treatment and new tools whose clinical applicability has been studied.

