### Aim

In line with the above, the main objective is to assess and analyse the effect of a muscle PT program on muscle condition and degree of sarcopenia, evaluating muscle strength, body composition and functionality in women over 65 years of age with sarcopenia probable, comparing it with a MT intervention and women who do not perform physical exercise.

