## Discussion

The study aims to investigate the impact of PT on older women at risk of sarcopenia. It is hypothesized that PT can reverse the probable sarcopenic state in women over 65 years of age, acting as an effective preventive therapy that eliminates the risk of sarcopenia and prevents its associated factors. Additionally, it is hypothesized that PT will significantly enhance functionality and body composition in comparison to other forms of exercise and no physical activity.

It is important to note that sarcopenia, which is commonly associated with frailty, is also independently linked to an increased risk of falls [45, 46]. By preventing sarcopenia, hospitalizations, institutionalizations, and other associated adverse effects can be indirectly avoided. The scientific community has demonstrated with high certainty that exercise programs reduce the rate and number of falls in the elderly [47]. Therefore, we expect both PT and other forms of exercise to improve this aspect, with a particularly optimistic expectation for PT.

Meta-analyses have been conducted to evaluate the effect of PT on healthy older adults [25, 26]. Similarly, meta-analyses have been performed to assess the impact of RT on function and body composition in people with sarcopenia [15, 48, 49]. However, this study is the first of its kind to investigate older women with probable sarcopenia according to EWGSOP2 diagnostic criteria. This study aims to address a gap in scientific knowledge by investigating an understudied area. To our knowledge, only one other clinical trial has evaluated the effect of RT in older women and men with probable sarcopenia. However, this trial only assessed appendicular lean mass and BF% [50].

This study investigates the effect of PT as a preventive treatment in older women with probable sarcopenia. It represents an important advancement in understanding and addressing this condition, as scientific evidence on the various forms of preventive treatment available for sarcopenia has been insufficient. However, this study’s findings will not only fill the knowledge gap but also support the recommendations issued by the EWGSOP2 in 2019. This will provide a solid basis for implementing effective prevention and treatment strategies for sarcopenia in older women [15].

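### The hypothesis is that power training beats both multicomponent training and no exercise, but the main test is a three-arm omnibus test that cannot show this, and no pairwise contrast is named as decisive

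*Protocol article*

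**What the plan says.** **The question.** The Aim sets PT against two comparators: "comparing it with a MT intervention and women who do not perform physical exercise". The abstract's Discussion expects that "PT will significantly improve functionality and body composition compared to other forms of exercise (MT) and no physical activity", and in the main Discussion "it is hypothesized that PT will significantly enhance functionality and body composition in comparison to other forms of exercise and no physical activity". This is a directed claim about two pairs of arms.

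**The test.** Under Data analysis, "multivariate analysis of variance (MANOVA) will be used as the main method", applied to a block of six functional variables and a block of seven body-composition variables. Three-group ANOVA or Kruskal-Wallis tests per variable then verify it. The rule for the biplot is "If the circles do not overlap, it can be concluded that there are significant differences between the groups", with no pair singled out. Pairwise tests follow last: "As an additional method, pairwise comparisons will be performed using Bonferroni’s test for normal and homogeneous variables", with Dunn's test otherwise. Their stated purpose is to locate which groups differ. The set of pairs is not restricted, so with three arms it is taken here to be all three.

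**The sizing.** The Sample size section names no pair either: "Assuming three groups, with an alpha risk of 0.05 and a beta risk of 0.2 in a bilateral contrast".

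**The concern.** The null hypothesis of the omnibus test is that all three arms are equal. It is false, and should be rejected, if only MT works, if PT and MT work equally well, or if PT is best. A significant main result therefore does not separate the trial's hypothesis from its rivals.

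The pairwise tests can separate them. But they rank as an additional method, and the protocol does not say whether PT versus MT, PT versus control, either or both must be significant before PT is called superior. These can point in different directions in the same data.

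The pairwise correction is also built to allow a claim on any of three pairs. The stated hypothesis requires two particular pairs to succeed together, and for that requirement no division of alpha is needed. At stake is whether the trial's conclusion about PT is fixed in advance, and how likely the trial is to support it if it is true.

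**Working it through.** **Inputs** (Sample size section): difference 2.5, SD 5, two-sided alpha 0.05, power 0.80, loss 20%, 105 women in ratio 1:1:1. That gives 105/3 = 35 per arm, and 35 × 0.8 = 28 after losses. Data analysis states intention to treat with last observation carried forward, which points to 35. The elimination criteria during the intervention leave this unclear, so both are shown.

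**The protocol's own figure.** n per arm = 2(z_alpha + z_beta)² × SD²/difference².
- At alpha 0.05: 2 × (1.960 + 0.842)² × 25/6.25 = 62.8, so 63. Then 63/0.8 gives 79 per arm, 237 in total.
- At 0.05/3: 2 × (2.394 + 0.842)² × 4 = 83.8, so 84. Then 84/0.8 = 105 per arm, 315 in total.

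A total of 105 is not reproduced by either calculation. This is not part of the point below.

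**1. What the omnibus test picks up.** Noncentrality = n × Σ(mean − grand mean)²/SD². For PT, MT, control = 2.5, 2.5, 0 the grand mean is 1.667 and the sum of squares is 0.694 + 0.694 + 2.778 = 4.167. Dividing by 25 gives 0.1667. Noncentrality is 4.67 at 28 per arm and 5.83 at 35. The noncentral F distribution gives power of 0.460 and 0.558. The means 0, 2.5, 0 (only MT works) and 2.5, 0, 0 (only PT works) have the same noncentrality and hence the same power. The test cannot tell them apart.

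Simulation of one-way ANOVA with pooled pairwise t tests (100,000 runs):

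| Means PT, MT, control | n per arm | Omnibus significant | PT > MT at 0.0167 | Omnibus significant, PT > MT not shown |
|---|---|---|---|---|
| 2.5, 2.5, 0 | 28 | 46% | 0.8% | 45% |
| 2.5, 2.5, 0 | 35 | 56% | 0.8% | 55% |
| 5, 2.5, 0 | 28 | 92% | 29% | 63% |
| 5, 2.5, 0 | 35 | 97% | 37% | 59% |

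A six-variable MANOVA with PT and MT each 0.5 SD better than control on every variable (3,000 runs; assumed correlation between variables 0.3 or 0.5) is significant in 51% or 35% of trials at 28 per arm, and 65% or 45% at 35.

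**2. Chance of showing PT better than both, when it is 2.5 better than both.** The standard error of a contrast is 5√(2/n): 1.336 at 28 and 1.195 at 35. The standardised effect is 2.5/1.336 = 1.871 and 2.5/1.195 = 2.092. Power for one contrast (normal approximation) at 28 is Φ(1.871 − 1.960) = 0.46 at alpha 0.05 and Φ(1.871 − 2.394) = 0.30 at 0.0167. At 35 these are 0.55 and 0.38. The two contrasts share the PT arm, so they are correlated 0.5. Joint power:

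| Alpha per contrast | 28 per arm, simulated (normal) | 35 per arm, simulated (normal) |
|---|---|---|
| 0.05/3 (three pairs) | 15% (16%) | 22% (22%) |
| 0.025 (two PT pairs, split) | 19% (20%) | 27% (28%) |
| 0.05 (both required) | 29% (30%) | 38% (39%) |

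**3. Is 0.05 for each contrast safe?** When PT = MT, both better than control, the both-required rule claims PT superiority in 2.2% of trials at 28 per arm and 2.4% at 35 (gain of 2.5), and in 2.5% and 2.4% (gain of 5). That is about the 2.5% expected in one direction of a two-sided 5% test. Requiring both contrasts supplies the protection, so no split is needed.

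**The case against.** Several points on the other side are sound.

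- **An omnibus test followed by corrected pairwise tests is conventional and valid for three arms.** This stands. The fault is the mismatch with the stated hypothesis.
- **The 46% and 56% are not false-positive rates.** This stands too. The omnibus null is false in that scenario and rejecting it is correct. The planned pairwise step would declare PT better than MT in under 1% of such trials. A reader might infer that the plan would pass off a general exercise effect as a success for PT. The documents do not support that: nowhere do they say a significant omnibus test establishes PT superiority, and the abstract's Methods lists pairwise comparisons beside MANOVA and ANOVA.
- **MT versus control has a purpose.** Design and setting treats PT and MT as two experimental groups, and Future perspectives gives an aim covering the effectiveness of both. A reader might infer that including this pair is simply wasted alpha. That goes too far. Its own cost is modest: joint power of 15% against 19% at 28 per arm, or 84 against 77 evaluable women per arm for 80% power on one contrast. Most of the gain comes from dropping the split altogether once both contrasts are required.
- **Ranking the contrasts could be left to a fuller document.** This is true of fine detail. But the article itself fixes which test is main and which is additional, and that order does not answer its own hypothesis.
- **105 equals the per-arm figure for three Bonferroni pairs with 20% loss.** A reader might infer that a per-arm number was reported as a total. The documents cannot confirm this, and the present point does not depend on it.

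**Conclusion.** The point holds. The omnibus test made the main method cannot establish that PT is better than both comparators, and the tests that could are ranked as additional, with no contrast named as decisive. All-pairs Bonferroni is valid but conservative for the joint claim: about 22% against 38% at 35 per arm, or 15% against 29% at 28, when PT is truly 2.5 better than both.

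These figures rest on the protocol's difference and SD, on three pairs (inferred), and on a single outcome compared across arms with SD 5 for the quantity analysed. They ignore baseline correlation and the grouping of women by senior centre, either of which would change the absolute values. Even 38% is low. That reflects the sample size, and this change does not cure it. The change is worth making before the data are analysed.

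**What to change.** In Data analysis, for 5STS and HG:

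1. Name PT versus control and PT versus MT as the deciding contrasts, each tested at two-sided 0.05. Claim superiority of PT over both only if both are significant in favour of PT. Use the same two contrasts if the rank-based branch applies.
2. If a claim on one contrast alone is also wanted, say how it is protected. A fixed sequence (PT versus control first, then PT versus MT only if the first succeeds) is one acceptable way, and it has the same joint power as requiring both.
3. Describe the MANOVA, biplot and three-group ANOVA or Kruskal-Wallis tests as supportive, and state that they do not by themselves establish PT superiority.
4. Keep MT versus control as a secondary comparison, reported with its confidence interval.

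**Cost.** Only the wording changes; data and software stay the same. MT versus control loses confirmatory status, and under a fixed sequence PT versus MT cannot be claimed if PT versus control fails. Error is controlled within each primary variable; multiplicity across 5STS and HG needs its own rule.
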